### Sample size calculation

According to our previous studies, on the basis of maintaining the original lipid-lowering therapy, in contrast with placebo, SMYA is expected to increase the plaque minimum fiber cap thickness (PMFCT) by an average of 40% µm. The standard deviation of the experimental group in the intervention of carotid plaque FCT is about 38, and the control group is about 36. This trial is designed as a 1:1 parallel control, α = 0.01, power = 90%, two-sided test, and the SAS (6.12) is adopted to evaluate the sample size. According to the calculation, 36 participants are needed for each group. After considering drop-out rates, the sample size of this protocol is 43 participants in the intervention group and the control group respectively, with a total of 86 cases.

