**Secondary outcome**

Plaque fiber cap volume, Volume percentage of fiber cap, LRNC volume, Volume percentage of LRNC, Internal bleeding volume of plaque, Internal bleeding volume percentage of plaque, Plaque calcification volume, Volume percentage of plaque calcification, Lumen stenosis rate, Average and maximum of vessel wall thickness, Vessel wall volume, Total vessel wall load (vessel wall volume/blood vessel total volume) will be measured at baseline (visit 1) and at the end of the treatment (visit 10), evaluated at the study endpoint.Carotid atherosclerosis score (CAS) [37] will be recorded at baseline (visit 1) and at the end of the treatment (visit 10), evaluated at the study endpoint.

i.Low risk: When MWT ≤ 2 mm, CAS = 1.ii.Medium and low risk: When MWT > 2 mm and LRNC ≤ 20%, CAS = 2.iii.Medium and high risk: When MWT > 2 mm and 20%< LRNC ≤ 40%, CAS = 3.iv.High risk: When MWT > 2 mm and 40%< LRNC, CAS = 4.
(3)hs-CRP, IL-1β, and IL-6 will be recorded at baseline (visit 1), during the treatment period (visit 2, 3, 4, 5, 6, 7, 8, 9 ) and at the end of the treatment (visit 10), evaluated at the study endpoint.(4)Blood lipid (TG, TC, HDL-C, LDL-C) and blood glucose will be recorded at baseline (visit 1), during the treatment period (visit 2, 3, 4, 5, 6, 7, 8, 9 ) and at the end of the treatment (visit 10), evaluated at the study endpoint.(5)Blood pressure and weight will be recorded at baseline (visit 1), during the treatment period (visit 2, 3, 4, 5, 6, 7, 8, 9 ), and at the end of the treatment (visit 10), evaluated at the study endpoint.

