### Statistical analysis plan

This study will adopt an intention-to-treat analysis. And statistical analysis will be conducted by special statisticians in a blind way. SAS (6.12) will be used for statistical analysis, all statistical tests are conducted by two-sided tests, and *p* ≤ 0.05 is regarded as statistically significant. We will first analyze the baseline balance to explain whether the intervention group and control group of basic conditions are comparable. Quantitative metrics will be described with a number of cases, mean, standard deviation, median, minimum, and maximum, and t test or Wilcoxon rank sum test will be adopted to compare two groups. Qualitative metrics will be listed in frequency and percentages, and chi-square test or Fisher’s exact test will be conducted to compare two groups. For the analysis of combined medication, we will list the number and percentage, and analyze the differences between the two groups by the chi-square test or Fisher’s exact test. Analysis of treatment compliance will list the number and percentage of cases with experimental drugs < 80%, > 120%, 80-120%, and chi-square test or Fisher’s exact test will be conducted. In terms of safety analysis, we will describe the incidence of AEs and SAEs during the treatment period, and list the detailed tables of AEs and SAEs.

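### The plan does not say which of its two test rules covers the ordered four-class carotid atherosclerosis score, and no listed test uses the recorded baseline class; a baseline-adjusted ordinal analysis would be more powerful

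*Protocol article*

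**What the plan says.** Under Secondary outcome, the protocol article states: "Carotid atherosclerosis score (CAS) [37] will be recorded at baseline". The timing given there is that it "will be recorded at baseline (visit 1) and at the end of the treatment (visit 10), evaluated at the study endpoint". The score takes the values 1 to 4, labelled from low to high risk; the second step reads "Medium and low risk: When MWT > 2 mm and LRNC ≤ 20%, CAS = 2". Classes 3 and 4 follow as the lipid-rich necrotic core (LRNC) share passes 20% and then 40%. Class 1 applies whenever maximum wall thickness is at most 2 mm, with no condition on LRNC.

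The Statistical analysis plan section has one rule for each data type:

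- Quantitative: "t test or Wilcoxon rank sum test will be adopted to compare two groups".
- Qualitative: "Qualitative metrics will be listed in frequency and percentages", and "chi-square test or Fisher’s exact test will be conducted to compare two groups".

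It adds that "all statistical tests are conducted by two-sided tests", with significance at p of 0.05 or less. It contains no rule for ordered categories, no mention of CAS and no baseline term in either rule.

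**The concern.** CAS fits either rule. It is a risk class with named grades, which suits the qualitative rule. It is also a numeric score, which suits the quantitative rule. The choice matters:

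- Chi-square and Fisher's exact test treat the four classes as unordered labels. A steady shift towards lower risk then counts no more than an erratic scatter of the same size.
- The t test uses order but takes the steps from 1 to 4 as equal.
- Wilcoxon uses order without assuming equal steps, but as listed it ignores where each participant started.

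The baseline gap is common to all four tests. Participants who start at CAS 1 cannot improve, and those who start at CAS 4 cannot worsen. A comparison that ignores baseline class leaves this variation in the error term. With 43 per arm, a real shift in risk class could go undetected although both measurements needed for a better analysis are already scheduled.

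**Working it through.** **Plan figure.** There is none for CAS. The sample size (36 per group, raised to 43) was set for minimum fibrous cap thickness with "1:1 parallel control, α = 0.01, power = 90%, two-sided test" and says nothing about CAS. The check therefore compares the tests with each other under declared assumptions.

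**Inputs.** From the documents: 43 per arm, two-sided 0.05, four ordered classes. Assumed: control classes at visit 10 of 25/35/25/15%, a treatment shift of 0.5 SD on a latent normal scale, and a baseline to visit 10 correlation of 0.5 to 0.7.

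**Step 1, class shares.** The cumulative shares 25, 60 and 85% give cut points z = -0.674, 0.253 and 1.036. Shifting by 0.5, the treated cumulative shares are Φ(-0.174) = 0.431, Φ(0.753) = 0.774 and Φ(1.536) = 0.938. The treated classes are thus 43.1/34.4/16.3/6.2%. The implied odds ratios at the three cuts are 2.27, 2.29 and 2.66; for example (0.431/0.569)/(0.25/0.75) = 2.27.

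**Step 2, chi-square.** Noncentrality = (n/2) Σ d²/p̄, where d is the difference in class share and p̄ the mean share. The four terms are 0.0960 + 0.0001 + 0.0363 + 0.0726 = 0.2050. Then 21.5 × 0.2050 = 4.41. On 3 degrees of freedom at 0.05 this gives power of 39%.

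**Step 3, Wilcoxon.** The probability that a treated participant has the lower class, counting ties as half, is 0.431 × 0.875 + 0.344 × 0.575 + 0.163 × 0.275 + 0.062 × 0.075 = 0.624. The standard error is √[(1 - Σp̄³)/(6n)] = √(0.909/258) = 0.0594. So z = 0.124/0.0594 = 2.09, and power is Φ(2.09 - 1.96) = 55%.

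**Step 4, adding baseline.** Simulation under the same inputs gives:

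| Analysis of CAS at visit 10 | Power |
|---|---|
| Chi-square | 35-40% |
| Wilcoxon | 53-56% |
| Wilcoxon stratified by baseline CAS | 62-73% |
| Proportional odds with baseline CAS | 65-75% |

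With no effect, each rejects in about 4-5% of runs. Steps 2 and 3 agree with the first two rows.

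**Step 5, other assumptions.** A second simulation used a common odds ratio of 2 or 3, a baseline correlation of 0.5 or 0.8, and four class distributions (25/25/25/25, 20/40/30/10, 10/60/20/10 and 50/30/15/5%), with 43 per arm. Ranges are over the distributions:

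| Odds ratio, correlation | Chi-square | Wilcoxon | Wilcoxon on change | Wilcoxon stratified by baseline |
|---|---|---|---|---|
| 2, 0.5 | 21-27% | 34-41% | 28-36% | 39-47% |
| 2, 0.8 | 20-29% | 34-43% | 45-62% | 52-69% |
| 3, 0.5 | 51-63% | 71-81% | 53-70% | 76-86% |
| 3, 0.8 | 51-61% | 69-78% | 77-95% | 89-98% |

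Setting by setting, chi-square loses 12 to 20 points against Wilcoxon and 18 to 40 against the stratified Wilcoxon. The stratified test gains 4 to 26 points over plain Wilcoxon, least at correlation 0.5. With no effect, all rejection rates lie between 4% and 6%. Fisher's exact test and the t test were not simulated.

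**The case against.** **The plan already lists an order-respecting test.** This is right. A reader might infer that the plan sends CAS to chi-square or Fisher and so discards much of its power. The documents do not support that: CAS is never assigned, it is written as a numeric score, and Wilcoxon is offered for quantitative data. The nearest hint the other way is that treatment compliance, once cut into three bands, goes to chi-square or Fisher, but that is only an inference. What stands is that the rule for CAS is open, and that even the better reading omits baseline class.

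**The tests could be applied to change from baseline.** The text does not say so. If they were, Wilcoxon on change falls 3 to 23 points below the stratified test in every setting of Step 5, and below plain Wilcoxon at correlation 0.5.

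**Such detail belongs in a separate analysis plan.** This is partly fair for one secondary outcome in a journal article, and silence on CAS alone would not be a finding. But the article does state its tests, and none of them uses baseline class.

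**The score has an odd step that no test cures.** Also right. A plaque with LRNC above 40% whose maximum wall thickness goes from 2.1 to 1.9 mm drops from CAS 4 to CAS 1. An ordinal model avoids assuming equal steps, but it still counts that participant as moving from the worst class to the best. A reader might expect the proposed analysis to remove this jump. It does not, because the jump is part of the score definition.

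**CAS carries little weight.** It is one of many secondary outcomes and was not powered. Maximum wall thickness and LRNC percentage are also secondary outcomes in their own right at the same visits.

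**Conclusion.** The point holds as a low-cost improvement to one secondary outcome. CAS is ordered and measured twice, the plan does not say which rule covers it, one permitted reading ignores order, and no listed test uses baseline class. Under the main assumptions, power rises from about 35-40% (chi-square) or 53-56% (Wilcoxon) to 62-75% with a baseline-adjusted ordinal analysis, at the same type I error.

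The direction was the same in every setting tried. The size depends on assumed class shares, effect and correlation, because the documents give none for CAS. Both simulations also assume a uniform shift along one underlying scale, which favours ordinal methods; class 1, defined without regard to LRNC, may not follow it. The primary outcome and its conclusion are untouched.

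**What to change.** Add one sentence to the Statistical analysis plan section: CAS at visit 10 is compared between groups by a proportional-odds model with treatment and baseline CAS as terms, reporting the common odds ratio with its 95% confidence interval; if the model does not fit, a Wilcoxon test stratified by baseline CAS is used. Chi-square, Fisher's exact and t tests are then not used for CAS. State beforehand how lack of fit is judged, so that the choice does not depend on the result.

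The cost is the sentence itself. Both CAS values are already scheduled at visits 1 and 10, so no new data, visits or participants are needed.

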### Subgroup analyses

We will conduct subgroup analysis on the primary outcome and secondary outcome according to whether participants are receiving lipid-lowering therapy.

## Discussion

Maintaining plaque stability is of great significance in inhibiting the progress of As and preventing CVD. High proportion of LRNC and thin fibrous cap are the main pathological features of VP. Fiber cap is caused by accumulation from an inflammatory cell-rich fatty streak damage [39, 40]. Erosion and fracture of the fiber cap may bring about ruptured plaque, causing acute fatal thrombosis eventually [41]. The rupture of VP is the direct cause of 60-80% of acute cardiovascular events [42]. In unstable patients, for instance, acute coronary syndrome (ACS), nearly all main coronary circulations are widely lesion showing multiple VPs, during ACS, the pan-coronary vulnerability can potentially derive from an arterial inflammation that is widespread [43]. A large number of inflammatory cytokines and proteases such as matrix metalloproteinases, macrophages, CRP, and IL-1 are found in ruptured plaque [44, 45], inflammation is an important factor leading to plaque vulnerability. These inflammatory factors and proteases may inhibit SMC proliferation, induce SMC and endothelial cell apoptosis, participate in endothelial cell denudation, inhibit collagen synthesis by SMC, and degrade collagen fibers, erode plaque fiber cap [43, 46]. Collagen synthesis decreases, but degradation increases, fiber cap becomes thin and fragile, which may aggravate the vulnerability and rupture of plaque. The development of inflammation theory has turned the goal of treating As to maintain plaque stability. Low-level host inflammation may be a crucial characteristic of unstable patients [43], reduce the level of inflammatory factors such as hs-CRP and reduce As inflammatory reactions may help to strengthen plaque stability. Targeted therapeutic drugs, for example, Canakinumab and Ziltivekimab, are expensive and have serious side effects, while cheap methotrexate is unable to effectively regulate arterial inflammation [47]. Under the background of clinical treatment deficiency, it is imperative to find a safe and effective treatment for plaque inflammation of As.

SMYA is a compound prescription of TCM. The four Chinese herbal medicines in it have potential effects on inhibiting inflammation, stabilizing plaque, and treating As. *Lonicera japonica* Thunb is the most important herb in SMYA formula, and can clearly inhibit the levels of hs-CRP in patients with carotid artery plaques [29]. Experimental studies have shown that the extract of *Scrophularia ningpoensis* Hemsl may remarkably reduce the level of inflammatory factors, such as TNF-α, IL-1β, and IL-6, in As model rats, regulating the excessive expression of NF-кB in arteries [48]. The active constituent of *Scrophularia ningpoensis* Hemsl, Scropolioside B, can decrease the expression of downstream IL-1β and other pro-inflammatory factors through NLRP3 inflammasome and has anti-inflammatory effects [49]. Coumarins, contained in *Angelica sinensis* (Oliv.) Diels, can lessen the content of NO, TNF-α, COX-2, and other inflammatory factors [50]. In As animal model, it was also found that the volatile oil of *Angelica sinensis* (Oliv.) Diels could improve the steatosis of liver cells, the damage of thoracic aorta intima and myocardial fibrosis, control vascular inflammatory reaction, and delay the formation of As plaque [51]. *Glycyrrhiza uralensis* Fisch has an effect on anti-inflammatory, immune regulation, and anti-tumor [52, 53]. The active ingredient contained in it may regulate NF-κB signal pathway and related inflammatory factors. For example, Hasan SK’s study indicated that 18-beta glycyrrhetinic acid inhibited the level of COX-2 and iNOS by down-regulating NF-κB [54]. Network pharmacology showed that the effective components of *Glycyrrhiza uralensis* Fisch could regulate cell proliferation and signal transduction of apoptotic cells through multiple signal pathways, such as PI3K-AKT, MAPK, and NOD, furthermore, regulate the release of inflammatory factors, thus affecting the As process [55]. Our previous research indicated that in ApoE-/- mice SMYA could prevent the degradation of collagen in plaque, increase the area of collagen, prevent pathological remodeling of blood vessels to a certain extent, and finally stabilize plaque [56]. Experimental research in vitro and in vivo has proved that SMYA might resist inflammation and delay the development of plaque, and have a potential therapeutic effect on As.

The recent development of HR-MRI techniques has made it possible to directly evaluate plaque component and stability [57–59]. Carotid HR-MRI is generally used to estimate the vascular wall and plaque structure. However, by the MR-VPD examination of combining contrast material enhanced T1-weighted imaging and carotid HR-MRI, we can correctly quantify the plaque structure as well, containing the LRNC and fibrous cap [60, 61]. To this day, MR-VPD examination is the only clinical vascular plaque analysis technology certified by the U. S. Food and Drug Administration (FDA) and the China FDA, combined with MRI-PlaqueView software can directly evaluate the vulnerability of plaque, is the best measure of internal quantitative characterization of plaque. [62, 63] Xia et al. study compared HR-MRI imaging of plaque with histopathology and indicated that the quantitative evaluation of LRNC in carotid plaque by MRI was highly close [64]. HR-MRI is safe and non-invasive, and can help effectively monitor plaque progression and carotid risk, besides, vascular imaging has high repeatability, which may greatly improve the prediction of stroke risk [65]. HR-MRI has become a reliable imaging method for monitoring the treatment of carotid plaque and has been used in many clinical trials [66, 67]. In this study, we will use MR-VPD of carotid HR-MRI to identify the PFC, LRNC, and other plaque components in participants to ensure the accuracy and objectivity of the trial results.

TCM has been used for more than 2000 years, and traditional prescriptions have received more and more attention [68]. The research about As anti-inflammatory treatment in China started relatively late, the high-quality research on TCM is still few, and the data of large-scale trials are lacking. So far, this is the first prospective double-blind TCM clinical trial to observe and treat As plaque by inhibiting inflammatory reaction directly. Simultaneously, the follow-up time is up to 50 weeks, which may helpfully observe the therapeutic effect of TCM. On the one hand, this trial assesses the efficacy of SMYA, on the other hand, carries out transcriptome analysis, proteomic analysis, and metagenomic analysis of blood and stool of subjects to explore the internal mechanism of SMYA that impacts As plaque.

In the “statin era”, targeting decreasing the inflammation burden is a necessary way to further reduce acute cardio-cerebrovascular events . Nevertheless, the cost of developing new specific anti-inflammatory medicaments is substantial, which is also a main obstacle to converting preclinical research into commercial As treatment [13]. Consequently, we have to effort to consider repurposing existing medicines with anti-inflammatory effects to solve the residual inflammatory risk cost-effectively. The use of TCM brings more possibilities for the treatment of As inflammation. We supposed that patients with As plaque would be improved from SMYA by inhibiting inflammation to enhance plaque stability, if successful, the finding will be greatly valuable in the treatment of As plaque and drug development.

### Trial status

This study is ongoing. The first patient was included on October 20, 2022, and the study is expected to be completed in December 2025.

## Data Availability

The raw data supporting the conclusions of this article will be made available by the authors [name], without undue reservation.

## Abbreviations

As: atherosclerosis
SMYA: Simiaoyongan Decoction
HR-MRI: high resolution magnetic resonance imaging
PMFCT: plaque minimum fiber cap thickness
CVD: cardiovascular diseases
IHD: ischemic heart disease
LRNC: lipid-rich necrotic core
MI: myocardial infarction
TCM: Traditional Chinese Medicine
CA: carotid artery
hs-CRP: hypersensitive C-reactive protein
NF-κB: nuclear factor kappa-B
TLR4: toll like receptor 4
Dll4: delta-like 4
IL-1β: interleukin-1β
TNF-α: tumor necrosis factor-α
COX-2: cyclooxygenase-2
LDL-C: low-density lipoprotein-cholesterol
HDL-L: high density lipoprotein-cholesterol
TG: triglyceride
TC: total cholesterol
SMC: smooth muscle cell
VP: vulnerable plaque
DHABUCM: Dongzhimen Hospital Affiliated to Beijing University of Chinese Medicine
AE: adverse event
ALT: alanine aminotransferase
AST: aspartate aminotransferase
BUN: blood urea nitrogen
Cr: creatinine
IMT: intima-media thickness
SAE: serious adverse event
CRF: case report form
CAS: Carotid Atherosclerosis Score
MWT: maximum wall thickness
ACS: acute coronary syndrome
MAPK: mitogen-activated protein kinase
MR-VPD: MR-vulnerable plaque diagnostics
FDA: food and drug administration
